## Abstract

Prognostication of neurodevelopmental outcomes for neonates with hypoxic–ischemic encephalopathy (HIE) is primarily reliant on structural assessment using conventional brain magnetic resonance imaging in the clinical setting. Diffuse optical tomography (DOT) can provide complementary information on brain function at the bedside, further enhancing prognostic accuracy. The predictive accuracy and generalizability of DOT-based neuroimaging markers are unknown. This study aims to test the feasibility of prospectively recruiting and retaining neonates for 12 months in a larger study that investigates the prognostic utility of DOT-based biomarkers of HIE. The study will recruit 25 neonates with HIE over one year and follow them beyond NICU discharge at 6 and 12 months of age. Study subjects will undergo resting-state DOT measurement within 7 days of life for a 30–45-min period without sedation. A customized neonatal cap with 10 sources and eight detectors per side will be used to quantify cortical functional connectivity and to generate brain networks using MATLAB-based software (version 24.2). The Ages and Stages Questionnaires—3rd edition will be used for standardized developmental assessments at follow-up. This feasibility study will help refine the design and sample-size calculation for an adequately powered larger study that determines the clinical utility of DOT-based neuroimaging in perinatal brain injury.

## 1. Introduction

Hypoxic–ischemic brain injury during the birth process is manifested as neonatal encephalopathy after birth, termed hypoxic–ischemic encephalopathy (HIE) [1]. Estimated to occur in 1–7/1000 live births [2], it is a significant cause of neonatal death and cerebral palsy, epilepsy, hearing loss, and visual impairment [3,4]. Induced therapeutic hypothermia initiated within six hours of birth substantially reduces risk of death and moderate–severe neurodevelopmental disability at 18 months, with a number needed to treat of 7 [5]. Unlike motor impairment, hypothermia does not reduce the risk of neurocognitive deficits that may not be evident until school age [6]. Even in the absence of cerebral palsy, neonates with HIE exposed to hypothermia therapy are at risk of having an IQ score of <70 (11%) or 71–84 (32%) at school age [7]. Although not as debilitating as cerebral palsy, abnormalities of cognitive functions, such as attention deficits, learning disabilities, and abnormalities of visuospatial processing and executive functioning, will have profound and long-lasting negative impacts on a child’s language skills, academic performance, and quality of life. Being able to anticipate the risk of neurologic deficits in early infancy, the crucial formative period of brain development, may facilitate early interventions and improve outcomes. Early developmental intervention programs may include targeted speech–language therapy, physical therapy, parental coaching, parent–infant relationship enhancement, infant stimulation, psychological therapy, sensory modulation, and biofeedback therapy [8,9,10,11].

Neurocognitive functions are challenging to prognosticate at early stages of life, and predictions based on conventional magnetic resonance imaging (MRI) brain images are often erroneous [12]. The neural correlate of higher-order cognitive functioning in early development remains largely unknown. Previous research has described the role of functional connectivity between cortical brain regions as an important determinant. For example, the prefrontal and parietal cortex neural networks may support attentional control abilities [13]. Altered structural and functional connectivity between key brain regions results in impairment of related cognitive functions [14]. Quantifying the functional connectome can shed light on brain reconfiguration following a birth injury during the first 2 years of life [14]. Traditionally, morphologic assessment of conventional brain MRI (T1/T2-weighted) and diffusion-weighted imaging (DWI) performed at 3–5 days of life has been used in clinical settings to aid clinical decisions and parental counselling [15]. However, caution is warranted when using conventional MRI to predict future cognitive outcomes. Recently, it was reported that among infants with no or minor injury on MRI, 34% develop moderate delay, and 5% develop severe delay at 24 months [16]. Furthermore, neurophysiological studies conducted during the neonatal period predicted later psychomotor impairment in infants with normal MRI results [12]. Currently, physicians primarily depend upon observing the infant’s behavior over time to prognosticate motor and cognitive outcomes, which are biased by practice setting and experience. Such perceptions are subjective and vulnerable to errors. Since physicians’ estimates of neurodevelopmental prognosis can influence parental counselling and early interventions, validated tools are needed to provide more objective estimates.

Diffuse optical tomography (DOT) is a non-invasive optical neuroimaging method that can be applied at the bedside to assess functional connections between brain regions [17]. It is an extension of fNIRS (functional near-infrared spectroscopy) that combines hemodynamic information from dense optical sensor arrays over a wide field of view. This technique utilizes near-infrared light to detect synchronous and spontaneous fluctuations in cerebral blood flow across different brain regions [18]. It combines cap-based multichannel data acquisition, such as electroencephalography (EEG), with spatial resolution high enough to create detailed cortical brain maps [19]. It helps quantify region-specific brain activity at rest, like functional MRI (fMRI). Advantages of DOT over fMRI include that it is portable, is lightweight, has high tolerance to body motion, does not produce noise, and does not require patient sedation. Moreover, fMRI is not routinely available in clinical practice, where conventional MRI images are commonly used for prognostication. The latter provides a qualitative assessment of brain injury rather than a functional assessment. Although DOT images are inferior to those acquired using fMRI in terms of spatial resolution, DOT provides biochemically specific, time-resolved, and spatially localized information on cerebral processes [20,21]. It is a reliable tool for evaluating cerebral oxygenation, with an intraclass coefficient of 0.7–0.8 [22,23,24,25,26]. The reproducibility of assessing brain networks was previously demonstrated [27]. The tool’s safety has been assessed in non-sedated term and preterm neonates at the bedside [28,29,30,31,32]. Therefore, DOT can be potentially used at the bedside as an adjunct to other currently available clinical prognostic markers.

DOT-based functional neuroimaging may provide early recognition of neural deficits at the bedside after several perinatal events such as premature birth, intraventricular hemorrhage, and birth trauma. This tool can be used to analyze the effects of bedside interventions and individualized care plans, such as music therapy, reading programs, sensory modulation techniques, and sleep, on the functional maturation of the developing brain. This study aims to conduct a single-center pilot project to assess the feasibility of a larger-scale study investigating the prognostic value of neonatal brain functional connectivity measures using DOT to predict long-term neurological outcomes. The primary objectives of this pilot study are to (i) demonstrate the feasibility of recruitment and retention strategies along with data collection methods in the NICU and (ii) assess the fidelity and safety of DOT measurements in neonates. The secondary objectives of this pilot study include (i) identifying logistic challenges, unexpected adverse effects, or technical difficulties, (ii) gaining stakeholder engagement, including parents and NICU nurses, and (iii) providing preliminary data on the variability of outcome measures to calculate the sample size of the larger trial accurately.

## 2. Materials and Methods

### 2.1. Study Design

This is a single-center, prospective observational cohort study. The study design conforms to the modified Standard Protocol Items: Recommendations for Interventional Trials (SPIRIT) [33].

### 2.2. Study Setting

This study will be conducted at the McMaster Children’s Hospital neonatal intensive care unit (NICU). The province of Ontario, Canada’s perinatal services are organized into three levels, namely the following: (i) Level 1: low neonatal risk, postnatal care of healthy newborn and resuscitation/stabilization of ill infants before transfer; (ii) Level 2: neonatal care for gestational age > 32 weeks and birth weight > 1500 g [exception: Level 2c > 30 weeks and >1200 g]; and (iii) Level 3: neonatal intensive care for any gestational age and birth weight, availability of subspecialty consultants, and surgical capability. Since therapeutic hypothermia resources are available solely in Level 3 hospitals in Ontario, Canada, neonates born across Level 1 and 2 hospitals are transferred to Level 3 with a specialized neonatal transport team [www.pcmch.on.ca, 2 June 2025]. McMaster Children’s Hospital is a Level 3 unit attached to a high-risk maternal and fetal medicine unit. Approximately 50–60 neonates per year are admitted to the NICU with the diagnosis of HIE; ~90% of them receive therapeutic hypothermia, and ~80% of them are outborn neonates. Outborn neonates may be born in any of the surrounding Level 1 or Level 2 hospitals in the catchment area of McMaster Children’s Hospital. When indicated, passive cooling is started in the referring hospital, and the neonate is transferred immediately to the Level 3 unit to receive hypothermia therapy using a servo-controlled device. A two-member in-house neonatal transport team facilitates the transfer of neonates from the referring center to the Level 3 NICU.

### 2.3. Therapeutic Hypothermia Protocol

Therapeutic hypothermia is the standard of care for moderate to severe HIE. The severity of encephalopathy is graded using a modified Sarnat Staging [34] based on 6 domains: level of consciousness, spontaneous activity, posture, tone, primitive reflexes (suck and Moros’ reflex), and autonomic nervous system (heart rate, pupils, and respiratory effort). At McMaster Children’s Hospital, a servo-controlled device, CritiCool^®^, Belmont Medical Technologies Ltd., Billerica, MA, USA, is used for neonatal hypothermia therapy. The infant is wrapped in a temperature-regulated cooling blanket to reduce core body temperature to 33–34 °C and maintained for 72 h using a rectal temperature probe for continuous monitoring. Then, the neonates are rewarmed to 36.5–37.5 °C over 6 h. Electrolyte levels, fluid balance, bleeding tendency, and cardiorespiratory functions are closely monitored during the therapy. Additionally, brain function is routinely monitored with continuous amplitude-integrated EEG or continuous video EEG until rewarming is completed to detect and manage seizures. All neonates will undergo structural brain MRI and MR spectroscopy on a 1.5 Tesla MRI scanner (Siemens Healthcare Limited, Forchheim Germany) at a median age of 3–5 days. MRIs conducted in the clinical setting include sequences T1W, T2W, DWI, SWI, and, if indicated, MRV/MRA. After discharge, all infants are followed in the Developmental Follow-Up clinic for 2–3 years to detect and treat developmental delays.

### 2.4. Research Ethics Approval

This study has been reviewed and approved by the Hamilton Integrated Research Ethics Board (HIREB #13982). The study was also registered on www.clinicaltrials.gov on 18 August 2022, and last updated on 3 October 2024 (NCT05514665). Any changes in protocol modifications will be communicated to the HIREB by the principal investigators.

### 2.5. Consent to Participate

All substitute decision makers for neonatal participants will provide written informed consent, obtained by a clinical research coordinator. Any modifications to the protocol that may impact the study’s intervention, target enrollment group, and outcomes will result in a formal amendment to the protocol.

### 2.6. Eligibility Criteria

Newborns admitted to the NICU will be enrolled if there is (i) evidence of an acute perinatal event, fetal metabolic acidosis, and a neurological exam indicative of encephalopathy, (ii) birth weight ≥ 1800 g, and (iii) gestational age at birth ≥ 35 weeks. The enrollment plan and exclusion criteria are illustrated in Figure 1.

### 2.7. Interventions

#### 2.7.1. Study Equipment

In this study, we will use a multichannel fNIRS system—the Brite MKII (Artinis Medical Systems, Einsteinweg, The Netherlands)—a wearable and flexible device designed to measure cerebral oxygenation. Each unit can record up to 27 channels, with sensors (comprising both transmitter and receiver elements) arranged on a recording cap. Two devices will be used concurrently to achieve comprehensive coverage of the neonatal scalp. By positioning channels across distinct brain regions, we can simultaneously monitor neural activity in these areas. Each transmitter optode incorporates light-emitting diodes (LEDs) that emit near-infrared light at wavelengths of 760 nm and 850 nm. These wavelengths are used to estimate changes in oxygenated and deoxygenated hemoglobin. The system operates in continuous-wave mode at a frame rate of 10 Hz. The imaging cap is engineered with preconfigured apertures for sensor placement, which connect to a compact unit weighing approximately 300 g. Data are acquired and stored on the device for subsequent analysis.

The equipment can be set up quickly, is robust against motion and environmental noise, has high resolution, and is silent, which makes it suitable for neonatal use. The device is comfortable due to its soft optodes and rubber optode holders, which provide optimized flexibility for testing within neonatal settings. The device uses non-ionizing radiation and is non-invasive. The optodes will be placed on the neonatal scalp for a maximum of 45 min. During this short application duration, the likelihood of skin irritation is minimal. The Brite MKII is not licensed in Canada but has been authorized by Health Canada as an investigational device only for this research study (Figure 2a,b).

#### 2.7.2. Experimental Setup

We made the customized neonatal cap stitched in 3 sizes to snugly fit head circumferences of 33 cm, 35 cm, and 38 cm (Figure 3). The cap could be slightly stretched in all directions, allowing us to accommodate multiple head sizes and shapes without affecting the channels’ positions that correspond to the anatomical landmarks of the brain. We determined the optode positions based on the 10–20 international EEG system [35] for electrode placement. Each transmitter–receiver pair had a 2 cm distance between them as specified by the device (Figure 4). The cap had 20 emitters and 16 detectors, with 27 channels per side covering the frontal, parietal, and occipital lobes (Figure 4).

We will first set up the cap by placing the transmitter and receiver optodes into the optode holders based on the cap layout. We will start recording to take measurements during natural sleep. All infants will be breathing spontaneously in room air. No sedation will be given to the infant. Parents will be encouraged to be at the bedside, and the infant will be cuddled in a warm blanket before being placed in the cot. All recordings will be taken within two hours after feeding in a dimly lit room in the NICU. The total duration of the resting-state data acquisition will range from 30 to 45 min, depending on the infant’s cooperativeness.

#### 2.7.3. Data Acquisition

Before initiating data acquisition, the fNIRS recording device will be prepared by establishing a high-fidelity wireless connection with OxySoft software (OxySoft 4) and ensuring the device is ready for measurement. The recording device and the computer will be placed on a hospital cart and brought into the NICU. The cart is positioned adjacent to the crib, and the fNIRS device will be set beside the patient (Figure 2b). Next, the NIRS cap will be placed on the patient’s head and adjusted so that the central optodes align with the nasion and all optodes are positioned perpendicularly to the scalp with adequate contact. Once the cap is secured, an automatic signal calibration will be performed. A brief video of the patient wearing the cap will be recorded to co-register the recording channels with brain regions.

OxySoft is proprietary software specifically designed for facilitating the collection, storage, visualization, and analysis of fNIRS data. It supports the parallel recording of multiple devices, enabling synchronized data acquisition from multiple fNIRS units. In this study, OxySoft version 4.0 will record, manage, export, and monitor data in real time during measurements. OxySoft provides data acquisition (DAQ) status and DAQ values during signal calibration and data collection, conveying information such as device status, recording time, total recording duration, and the amount of light detected in each fNIRS recording channel. Channels whose light levels exceed or fall below acceptable thresholds are highlighted in red. Such out-of-range values may arise from head movements that displace the cap, environmental noise, or the presence of hair between the optode and the skin. If this occurs during signal calibration, the cap will be readjusted to optimize optode–scalp contact and calibration will be repeated until the light levels fall within the acceptable range. The research team will continuously monitor the DAQ values throughout the study.

#### 2.7.4. Neuroanatomy

The proposed study examines the interactions between different brain regions in neonates. Intrinsic brain activity at rest without a stimulus can provide information on resting-state functional connectivity, which yields Resting-State Networks (RSNs) [36]. Previously identified canonical RSNs in term neonates are located in primary motor and sensory cortices (sensorimotor), medial aspects of the occipital cortex (visual), the temporal lobe and inferior parietal cortex (auditory), and the association cortex (pro-default mode networks) [37,38]. The region of interest (ROI) will be defined manually on the age-specific templates by visual inspection using specific atlases of human brain development. From these ROI positions, seed time traces will be extracted for the three hemodynamic contrasts (HbO2, HbR and HbT). These time courses will then be correlated with every other voxel within the field of view to generate correlation (r) maps.

#### 2.7.5. Principle

DOT utilizes the absorption of infrared light by oxygenated and deoxygenated hemoglobin to measure changes in cortical blood flow, which indexes localized neural activity (Figure 5). This indirect measure of neural activity is similar to that used in fMRI, which has been widely used in adult and child neuroimaging studies based on neurovascular coupling. Neurovascular coupling refers to the process of the brain regulating blood flow in response to neural activity, which is a mechanism of ensuring there is enough oxygen to support higher-activity brain regions. Functional connectivity measures enable the determination of the relationship between neural demand and neurovascular coupling [39]. Therefore, measuring regional blood flow can provide information about the brain’s regulatory response to injury in the context of HIE. Near-infrared light is absorbed by oxygenated and deoxygenated hemoglobin in the cerebral vascular bed. A transmitter (source) emits light of a specific wavelength. The light passes through the cerebral vascular bed to be captured in a receiver (detector), which is also placed on the scalp’s surface. Standard light absorption properties of oxy- and deoxyhemoglobin are then used to calculate the amount of oxy- versus deoxyhemoglobin in the cerebral vascular bed. These values indirectly provide a measure of cerebral blood flow in different regions of the brain. Using the above principle, the raw fNIRS data collected are then processed through designated software to map the brain’s active and inactive regions in a stipulated time period. These assessments can be conducted at rest and in response to specific stimuli such as sound or light.

### 2.8. Objectives and Outcomes

#### Objectives and Corresponding Outcomes of the Feasibility Trial

Objective 1: To determine the feasibility of recruitment and retention strategies and data collection methods in the NICU. Feasibility will be assessed by reporting the following metrics: (i) The recruitment rate will be reported to assess the ability to recruit the target population within the desired timeframe, determined by the number of eligible participants who are enrolled in the study. We will maintain a recruitment tracking log. (ii) The follow-up rate will be used to assess the ability to retain participants and complete follow-up assessments, as determined by the percentage of enrolled patients who complete follow-up at 12 months. We will maintain a record of participant follow-up procedures and dropout rates. (iii) The rate of missing data will be determined by the percentage of completed data fields measured by reviewing collected data to identify any missing information, inconsistencies, or incomplete responses. *Criteria for Feasibility:* The main study will be feasible if the pilot study is successful based on the predefined criteria: (i) 80% of the eligible patients consent to the testing; (ii) 90% of the consented participants get DOT measurements taken before 7 days of life; (iii) for 80% of the consented participants, parent-reported developmental assessment is available at 6 and 12 months.

Objective 2: To assess the fidelity and safety of DOT measurements in neonates. (i) Safety will be assessed by reporting any adverse skin reactions to sensors or excessive agitation in the neonate, requiring early termination of the study. (ii) Data quality will be assessed by recording the degree of the signal-to-noise ratio. We will keep a record of the ability to properly place sensors with good contact and the ability to minimize motion artifacts and ambient light interference in each subject. (iii) Ability to complete adequate data acquisition within 45 min. *Criteria for Feasibility:* Time required for resting-state data acquisition per infant < 45 min.

Objective 3: To identify logistic challenges, unexpected adverse effects, or technical difficulties. Operational feasibility will be assessed based on the time and personnel required for each stage of the study, as well as the logistical challenges.

Objective 4: To gain stakeholder engagement, including that of parents and NICU nurses. The research team will also approach parents and bedside nurses at the end of the NICU stay with a brief survey to gather their perceptions about the study procedures. The survey consists of three questions: (1) Parents Section: Please let the study investigators know if you had any concerns during the DOT measurements of your child: (a) it takes a long time to measure, (b) the infant feels discomfort, (iii) others (free text), (iv) none. (2) Nursing Section: Please let the study investigators know if you had any concerns during the DOT measurements of your patient: (a) any concern from nursing staff about interfering with infant sleep, (b) interfering with the infant feeding schedule, (c) causing discomfort to the infant, (d) taking a long time, (e) the need for the nurse to be at the bedside, (f) others (free text), and (g) none.
Secondary objectives include the following:

Objective 5: To provide preliminary data on outcome measures to calculate the sample size of the adequately powered study. Clinical outcomes of the definitive trial will be measured to assess the reliability of data collection tools. Short-term neurological outcomes of neonates with HIE will be assessed using a brain MRI conducted within 7 days of life. The severity of brain injury on the MRI brain will be quantified using a detailed scoring system. The MRI score consists of 4 subscores, including grey matter (basal ganglia, thalamus, PLIC, brainstem, perirolandic cortex, and hippocampus), white matter/cortex (including optic radiation and corpus callosum), and cerebellum. Each category is weighted by its degree (0 = no injury; 1 = focal or <50%; 2 = extensive or >50%) and its location (1 = unilateral; 2 = bilateral). Additional scores are added if there is an intraventricular hemorrhage, subdural hemorrhage, or sinovenous thrombosis (score of 1 each if present). The final score represents a summation of all 4 subscores (maximum grey matter subscore 23, maximum white matter subscore 21, maximum cerebellum subscore 8, and maximum additional subscore 3), with 2 additional scores being added when H-MRS is performed in the basal ganglia and thalamus (score of 1 each if present: reduced N-acetyl aspartate (NAA) peak and increased lactate peak). This adds up to a maximum score of 57 [40].

Long-term neurological outcomes will be measured with a validated parent-reported questionnaire at 6 months and 12 months of age. We will use the Ages and Stages Questionnaire—3rd edition (ASQ-3) to assess five areas of childhood development—Communication, Gross Motor, Fine Motor, Problem-Solving, and Personal–Social—through parent/caregiver reports. Filling in the report takes 10–15 min, and it takes 2–3 min to score. The ASQ-3 is a widely used screening measure and has proven to be an effective developmental screening tool in cross-cultural populations [41]. The questionnaire includes 30 items, scored as yes, sometimes, or not yet, on questions about a child’s ability to perform a task [42]. The concurrent validity of the ASQ-3 with standardized testing of developmental (Bayley Scales of Infant Development) and intellectual (Stanford–Binet Intelligence Test–4th edition) skills has been demonstrated [43]. The ASQ-3 has a sensitivity of (0.70–0.90) and specificity of (0.76–0.91) in detecting developmental impairment, with retest reliability of (0.94–0.95) and interrater reliabilities between parents and professionals of (0.94–0.95) [44,45]. We will also use the Ages and Stages Questionnaire: socioemotional-2 (ASQ: SE-2) to perform a broadband social–emotional screening for study participants. Social–emotional domains include self-regulation, compliance, social communication, adaptive functioning, autonomy, affect, and interaction with people. ASQ: SE-2 test characteristics reflect an overall sensitivity of 81% across age intervals and an overall specificity of 84% across age intervals, with 89% test–retest reliability and 84% internal consistency [46]. Table 1 summarizes the study objectives, outcomes and corresponding data analysis. 

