### 2.10. Sample Size and Recruitment

The National Center for Complementary and Integrative Health notes that sample size should be based on practical considerations, including participant flow, budgetary constraints, and the number of participants needed to reasonably evaluate feasibility goals [47]. Hence, for this work, a sample size of 25 was considered adequate to reach saturation and establish feasibility. If the feasibility criteria are met, the sample size for the larger trial will be determined based on the data analysis.

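### The DOT window is given as 7 days in the abstract and feasibility criterion but as days 4–15 in the participant timeline, so an on-schedule recording can count against a primary feasibility criterion

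*Protocol article*

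**What the plan says.** The article gives the timing of the DOT measurement in four places.

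- **Abstract:** "Study subjects will undergo resting-state DOT measurement within 7 days of life".
- **Section 2.8, Objective 1, criteria for feasibility:** "ii) 90% of the consented participants get DOT measurements taken before 7 days of life".
- **Table 1, first primary aim:** the same criterion in the same words.
- **Table 2, participant timeline:** the only mark in the DOT row is under days 4–15. A separate column for days 4–7 exists and holds the brain MRI.

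The criterion has consequences. Section 2.8 states: "The main study will be feasible if the pilot study is successful based on the predefined criteria". Section 2.10 adds: "If the feasibility criteria are met, the sample size for the larger trial will be determined based on the data analysis". On the number of infants, Section 2.10 says that "a sample size of 25 was considered adequate to reach saturation and establish feasibility".

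**The concern.** Table 2 is the schedule that site staff would work from, and it allows DOT on days 8–15. A recording on those days keeps to the timeline, yet it contradicts the abstract and counts as a miss under a criterion that helps decide whether the main study is feasible. If the criterion is missed, the report could not say whether early recording was impracticable or whether staff had simply used the time that Table 2 gave them.

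There is a smaller inconsistency over day 7. The abstract's *within* appears to include a recording on day 7, while the criterion's *before* appears to exclude it.

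**Working it through.** The plan has no calculated figure to reproduce here. The sample size of 25 rests on practical considerations, without a formula or precision target. The check is a comparison of the passages, followed by the arithmetic of the criterion.

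**1. Is the Table 2 reading sound?** Matching each mark to its column puts hypothermia under days 1–3, MRI under days 4–7 and both ASQ instruments under 6 and 12 months. These agree with Sections 2.3 and 2.8. Only DOT disagrees with the text, so a column shift in the extracted table does not explain it.

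**2. How do the windows overlap?** Days 4 to 15 are 15 − 4 + 1 = 12 calendar days.

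| Day of recording | Table 2 | Abstract | Criterion (ii) |
|---|---|---|---|
| 4–6 (3 days) | on schedule | met | met |
| 7 (1 day) | on schedule | met | depends on how *before* is read |
| 8–15 (8 days) | on schedule | not met | not met |

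Table 2 does not say whether its days count from birth or from allocation, which it labels Day 0. If they count from allocation, postnatal age at DOT is the same or greater, so the conflict remains.

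**3. How many late recordings does the criterion tolerate?** 0.90 × 25 = 22.5, so 23 infants are needed. 23/25 = 92% meets the criterion and 22/25 = 88% does not. Two late recordings are tolerated and three fail it.

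**4. How sensitive is the result?** The documents give no timing distribution, so the late share q is an assumption. Suppose that all 25 infants are recorded within the Table 2 window and are late independently with probability q. The chance of meeting the criterion is then

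P(X ≥ 23) = Σ (k = 23 to 25) C(25, k) (1 − q)^k q^(25 − k).

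For q = 0.10: 300 × 0.9^23 × 0.01 + 25 × 0.9^24 × 0.1 + 0.9^25 = 0.266 + 0.199 + 0.072 = 0.537.

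| Late share q (assumed) | Chance of meeting the criterion |
|---|---|
| 2% | 0.99 |
| 5% | 0.87 |
| 10% | 0.54 |
| 15% | 0.25 |
| 20% | 0.10 |
| 30% | 0.01 |

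**The case against.** The best defence is that the two windows do different jobs. Table 2 would be the period in which a recording is accepted, and criterion (ii) a stricter test of timeliness within it. A pilot may properly accept later recordings and still ask whether 90% can be made early; on-schedule recordings that miss the target are then how such a measure works. This is a legitimate design, but the article does not state it. It also does not fit the abstract, which gives the 7-day limit as the procedure for all subjects and not as a target. The objection therefore shapes the remedy without removing the inconsistency.

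The objection also limits what may be concluded. Four stronger readings are tempting, and the documents do not support them.

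- **A reader might infer that the scoring of the criterion is itself in doubt.** It is not. Section 2.8 and Table 1 word it identically, with one cut-off apart from the day-7 question. What Table 2 can change is when staff record.
- **A reader might spread recordings evenly over days 4–15 and conclude that the criterion is almost certain to fail.** Nothing in the article suggests even timing, and a team with a stated 7-day aim could do much better.
- **A reader might object that the early window is too tight for cooled infants,** since Section 2.3 gives 72 h of cooling and 6 h of rewarming, 78 h in all. Whether 90% can be recorded in the time left is what the pilot is meant to find out.
- **A reader might infer that mixing earlier and later recordings spoils the brain metrics.** The documents give no evidence that this age spread matters. Those analyses are exploratory secondary aims, and Section 4 already warns about associations in a small sample.

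**Conclusion.** The concern holds as an internal inconsistency. Three statements point to 7 days and Table 2 points to days 4–15, with nothing to reconcile them. A recording on days 8–15 complies with Table 2, contradicts the abstract and counts against a primary feasibility criterion.

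What follows from the text alone is that 23 of 25 infants must be on time and that three late recordings fail the criterion. The probabilities, from about 0.87 at 5% late to about 0.10 at 20% late, rest on an assumed late share, independence between infants and a recording for every infant. They show that a modest late share could decide the result; they do not predict it. The documents do not show which window was intended, and this review does not say which is right.

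**What to change.** Reconcile the passages before any data are read, in one of two ways.

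1. State one DOT window, say whether day 7 counts, and use it unchanged in the abstract, criterion (ii), Table 1 and Table 2.
2. If a wider permitted window is intended, say so explicitly, bring the abstract into line, and keep the cut-off in criterion (ii) as a separate timeliness target, again with the status of day 7 stated.

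In either case, say whether the days in Table 2 count from birth or from allocation. Keep all consented infants in the denominator of criterion (ii), as it is now worded. Count recordings outside the criterion's window as not meeting it, and also report how many there were and the postnatal age at DOT of each. A reader can then tell late recordings from absent ones.

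The cost is a few lines of text and one table entry, plus the age at recording. No extra infants or procedures are needed.
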